#### Phase 2: Beta Testing and Feasibility Trial With Exit Interviews

##### Beta Testing

After screening, consent, and enrollment, up to 10 individuals with COP will beta test *the Face-Forward-Web* intervention. The research coordinator will schedule an orientation session, in which she will outline how to navigate the *Face-Forward-Web* platform. Participants will then independently complete the intervention. After each module, participants will be asked to indicate their level of satisfaction from the module on a 1-4 Likert scale and provide feedback on their impressions from the module in a textbox. At the conclusion of the intervention, participants will participate in exit interviews over Zoom. Exit interviews will last ~30 minutes and will be audio-recorded and transcribed. Similar to phase 1, the exit interviews will involve a semistructured script, followed by rapid data analysis and qualitative thematic analysis using NVivo 12. We will utilize results to further refine the intervention’s content manual and procedures as well as refine *Face-Forward-Web* prior to the feasibility trial.

##### Feasibility Testing

Participants will be recruited, screened, and enrolled using the methods described above. After consenting, participants (n=up to 20) will complete a set of valid and reliable online questionnaires over the secure Research Electronic Data Capture (REDCap) system. The estimated time for completion is 20 minutes. If participants miss an item, they will be prompted to complete it, thereby minimizing missing data. Participants will complete the questionaries at 2 additional timepoints—after completing the intervention and again 3 months later. After baseline assessments, participants will participate in an orientation session. Then they will complete the intervention and subsequent exit interviews following similar procedures as in the beta testing.

### The Face-Forward-Web Intervention

*Face-Forward-Web* consists of 5 sessions (Table 1), which teach relaxation (eg, body scan, deep breathing), mindfulness, and cognitive-behavioral skills (eg, adaptive thinking, reducing negative affective reactivity). The content is consistent with *GetActive* [44] and adapted to the unique needs of people with COP and for delivery via the web platform. Due to the individual/asynchronous format of *Face-Forward-Web*, we were able to condense the *GetActive* content into 5 sessions, which may maximize feasibility and engagement (to be tested in the proposed studies). Each session consists of a combination of short (~5-10 minutes) videos conveying educational content and skill delivery. Each session ends with an interactive quiz covering the session’s content to gauge comprehension and facilitate material absorption, which can be an effective intervention element for people with chronic pain [51]. Audio and video clips will be available to guide participants through their daily home practice. Once invited by a research assistant, participants will log in and access the first session’s materials. Contingent on completion of the interactive quiz at the end of each session, access to the subsequent session will be granted in the following week. Participants will be free to review and practice all the skills and materials from the completed sessions until the 3-month follow-up assessment and will be encouraged to use the platform for daily practice. The platform will be easily accessible across multiple interfaces such as a website and mobile app through any internet-enabled device (eg, smartphone, tablet, computer). We will track participants’ homework completion and platform activity. To encourage retention, we will text reminders about the sessions and home practice through the Health Insurance Portability and Accountability Act–compliant texting service, as previously successfully implemented by our group and deemed useful by participants [52].

**Table 1 table1:** Face-Forward-Web session topics and examples of content.

Session	*Face-Forward-Web* topic	Skills and examples of content/videos
1	Taking charge of orofacial pain	Orofacial “Pain alarm” (reactions to COP^a^) Debunking myths about COP Downward and upward spirals (COP is associated with thoughts, feelings, and behaviors that can be maladaptive or adaptive) Deep breathing
2	Managing emotional challenges in orofacial pain	Mindfulness Body scan
3	Working with negative thoughts	Identifying NATs^b^ Checking NATs Challenging NATs
4	Not letting orofacial pain get the best of us	Acceptance Using Face-Forward-Web skills to reengage in activities (eg, daily, recreational, social, family, work-related)
5	Facing forward: “Rolling” with orofacial pain and staying resilient	Mindfulness of discomfort and pain Review all skills Create personalized plan

^a^COP: chronic orofacial pain.

^b^NAT: negative automatic thought.

### Treatment Delivery and Protocol Adherence

Participants will continue their usual care as determined by their medical providers (eg, medication, occlusal splits and adjustments, physical therapy). We will determine fidelity to *Face-Forward-Web* via a user experience software such as Google Analytics [53]. This will enable us to track participants’ frequency and time spent on each of the web platform’s pages and clicks on exercises and quizzes and evaluate participation, even on partially completed sessions, thereby increasing the accuracy of attendance evaluation.

### Assessments

#### Pain Severity and Pain Interference

The Graded Chronic Pain Scale [54] is a 7-item scale measuring pain severity and pain interference. The time frame of reference will be the past week, consistent with prior work [55,56]. The Numerical Rating Scale [57] is a single item measure assessing pain severity.

#### Anxiety

The Generalized Anxiety Disorder Scale [58] is a 7-item scale that assesses the severity of the anxiety symptoms over the past 2 weeks.

#### Depression

The Patient Health Questionnaire [59] is a 9-item measure that assesses depression symptoms over the past 2 weeks.

#### Catastrophic Thinking About Pain

The Pain Catastrophizing Scale [60] is a 13-item measure assessing hopelessness, helplessness, and rumination about pain.

#### Fear of Pain Due To Movement

The Tampa Scale for Kinesiophobia for Temporomandibular Disorders [61] is a 12-item scale assessing fear of pain due to facial movement and adapted to heterogeneous orofacial pain [62] (ie, expanding references from “jaw” to “jaw or face”)

#### Mindfulness

The Cognitive and Affective Mindfulness Scale-Revised [63] is a 12-item questionnaire that measures an individual's level of mindfulness, including present-focused attention, awareness of thoughts and feelings, and nonjudgmental acceptance of internal experiences. The Applied Mindfulness Process Scale [64] is a 15-item questionnaire that measures respondents’ application of mindfulness practices in daily life.

#### Treatment Satisfaction

The User Experience Questionnaire assesses users’ satisfaction and experience with digital products, software, and platforms [65]. This assessment is administered at 1 timepoint, immediately after the intervention.

#### Treatment Credibility

The Credibility and Expectancy Questionnaire assesses how believable and logical patients perceive the treatment to be [66]. This assessment is administered at 1 timepoint, immediately after the intervention.

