**Methods:**

We will accomplish these aims in 2 phases, incorporating user-centered design principles. For phase 1, we conducted semistructured focus groups (n=4 groups, 22 participants) with individuals with COP. We are using rapid data analysis followed by thematic analysis to gauge treatment needs, preferences, and perceptions of the proposed platform and skills. This information will inform session structure and content as well as development of a wireframe followed by a prototype. For phase 2, we will conduct beta testing (up to n=10) followed by a feasibility trial (up to n=20) with exit interviews to gather feedback. The primary outcomes are feasibility benchmarks such as recruitment (≥70% of the eligible participants will participate), acceptability (≥70% of the participants complete ≥4 or 5 sessions), credibility, expectancy (≥70% above the Credibility and Expectancy scale’s midpoint), and satisfaction (≥70% above the User Experience Questionnaire’s midpoint).

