## Methods

### Study Design and Setting

This study protocol adheres to the SPIRIT (Standard Protocol Items: Recommendations for Interventional Trials) 2013 statement (Multimedia Appendix 1). Our approach is consistent with the National Institutes of Health (NIH) stage model for behavioral intervention development [47,48]. The proposed phases address stages 1A (intervention development and refinement) and 1B (feasibility testing). For phase 2, the primary outcomes are feasibility benchmarks (ie, feasibility of recruitment, credibility and expectancy, acceptability of treatment, adherence to homework, satisfaction [user experience], feasibility of assessments, adverse events).

This study will be completed in 2 main phases conducted at a large academic hospital. In phase 1, we conducted 4 virtual focus groups (22 patients with COP) at which point we reached saturation [49]. We aimed to understand their treatment needs and preferences, perceptions, and recommendations for a web platform delivery, and the best ways to engage and retain participants. We also gathered participants’ feedback on program content via sample videos similar to those intended to be used in the *Face-Forward-Web* program. We are using this information to inform adaptations from the *GetActive* intervention for chronic musculoskeletal pain intervention to the *Face-Forward-Web* intervention for chronic orofacial pain as well as for the development of a wireframe for *Face-Forward-Web*, followed by a prototype [42].

In phase 2, we will conduct beta testing (up to n=10) and revise *Face-Forward-Web* and the study procedures according to the feedback and information gathered. We will then conduct a feasibility trial (up to n=20) with rapid iterative development of the prototype intervention [50].

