#### Phase 2: Beta and Feasibility Testing With Exit Interviews

We will use frequency and proportions to assess the feasibility of the recruitment and retention procedures. We will determine treatment satisfaction and credibility by the proportion of participants who score above the scale midpoint in the User Experience Questionnaire [65] and Credibility and Expectancy Questionnaire [66], respectively. See Table 2 for further details on the feasibility, credibility, and acceptability benchmarks, consistent with other established feasibility work [67-69]. We will analyze qualitative data from the exit interviews by using the same procedures described in phase 1.

**Table 2 table2:** Feasibility benchmarks.

Outcome	Acceptable	Excellent
Credibility and expectancy	>70% of the participants with score over scale midpoint.	>75% of the participants with score over scale midpoint.
User experience	>70% of the participants with score over scale midpoint.	>75% of the participants with score over scale midpoint.
Feasibility of recruitment	>70% of eligible participants agree to participate.	At least 80% of eligible participants agree to participate.
Acceptability of treatment	>70% of the participants attend 3 out of 5 sessions.	>80% of the participants attend 3 out of 5 sessions.
Adherence to homework	>70% of the participants practice >1 skill on 3 d/wk.	>80% of participants practice >1 skill on 3 d/wk.
Feasibility of assessments	>70% of the participants have no measures fully missing.	>90% of the participants have no measures fully missing.
Adverse events	Minimal	None

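### Credibility and expectancy, a primary benchmark, is rated only once and only after the intervention, so it cannot measure prospective expectancy and may miss people who stop early

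*Protocol article*

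**What the plan says.** The Treatment Credibility paragraph under Assessments fixes the timing of the Credibility and Expectancy Questionnaire: "This assessment is administered at 1 timepoint, immediately after the intervention". The same paragraph describes the instrument by its credibility content alone: "The Credibility and Expectancy Questionnaire assesses how believable and logical patients perceive the treatment to be". The Treatment Satisfaction paragraph gives the User Experience Questionnaire the same single timepoint.

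The outcome is primary. Study Design and Setting lists, among the phase 2 primary outcomes, "feasibility of recruitment, credibility and expectancy, acceptability of treatment, adherence to homework". The abstract gives the criterion as "credibility, expectancy (≥70% above the Credibility and Expectancy scale’s midpoint". Table 2 sets the acceptable level at ">70% of the participants with score over scale midpoint" and the excellent level at more than 75%, with identical levels for user experience.

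Two further statements bear on who will be asked. Feasibility Testing has a baseline battery and then says: "Participants will complete the questionaries at 2 additional timepoints—after completing the intervention and again 3 months later". The section on the intervention says: "Contingent on completion of the interactive quiz at the end of each session, access to the subsequent session will be granted in the following week".

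**The concern.** Expectancy, in its ordinary sense, is what a person expects a treatment to do, so it has to be asked before the person knows what the treatment did. Asked once the sessions are over, the item can reflect whether the participant felt better and liked the platform. The trial would then report a primary outcome named expectancy without having measured it. Two benchmarks with the same thresholds, taken at the same moment, could both be carried by one general impression.

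There is also a question of who answers. A participant who finds the rationale unconvincing has a reason to stop, and someone who stops may never reach an assessment placed after completion. If those people drop out of the denominator, the benchmark becomes easier to pass for a reason unrelated to how credible the programme is. The results are meant to inform a later efficacy trial against an active control platform, and an early expectancy rating cannot be recovered once phase 2 has run.

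**Working it through.** The document gives no calculation for this benchmark, so there is no stated figure to reproduce. The check has three parts.

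**1. Timing.** Every mention of the questionnaire was compared: the abstract, Study Design and Setting, the Treatment Credibility paragraph, and Data Analysis with Table 2. Only the Treatment Credibility paragraph states when it is given. The statement in Feasibility Testing about repeated questionnaires does not add an earlier credibility rating, because the specific paragraph limits this scale to one timepoint.

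**2. What the threshold demands if only completers are counted.** Inputs: up to 20 enrolled (Study Design and Setting) and a threshold of more than 70% (Table 2). Assumption: m completers are scored and early stoppers are left out. The smallest passing count is the smallest whole number x with x/m > 0.70.

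| Scored (m) | Needed (x) | x/m | (x−1)/m, fails | x as share of 20 enrolled |
|---|---|---|---|---|
| 20 | 15 | 75.0% | 70.0% | 75% |
| 18 | 13 | 72.2% | 66.7% | 65% |
| 16 | 12 | 75.0% | 68.8% | 60% |
| 15 | 11 | 73.3% | 66.7% | 55% |
| 14 | 10 | 71.4% | 64.3% | 50% |

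Under the abstract's wording (at least 70%), only the first row changes: 14 of 20 would pass. The other counts stay the same.

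**3. How far selective stopping could move the observed share.** Let b be the share of all enrolled who would score above the midpoint at the start, and r1 and r0 the retention of those above and not above it. If scores do not otherwise change, the share among those retained is b·r1 / (b·r1 + (1−b)·r0). The document gives none of these values; all are assumptions.

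- b = 60%, retention 90% against 60%: 0.54 / (0.54 + 0.24) = 69%.
- b = 60%, retention 95% against 50%: 0.57 / (0.57 + 0.20) = 74%.
- b = 65%, retention 90% against 60%: 0.585 / (0.585 + 0.210) = 74%.
- b = 65%, retention 95% against 50%: 0.6175 / (0.6175 + 0.1750) = 78%.
- b = 60%, retention 80% in both: 0.48 / (0.48 + 0.32) = 60%, no shift.

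A share that fails the benchmark can therefore be observed as a pass, and in the fourth case as excellent, but only if stopping is related to credibility and stoppers are not counted.

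**The case against.** The strongest reply is that the document never says only completers are scored. Table 2 speaks of participants, and nothing excludes assessing people who stop early or counting them as not above the midpoint. A denominator is also something an article commonly leaves to the full protocol or analysis plan. This stands. A reader might infer that the benchmark is biased upward by design, but completer-only scoring is an inference from the schedule and the quiz gating. The gap in the table comes from the denominator, not from the timing as such: with all 20 enrolled in the denominator and stoppers counted as failures, it disappears.

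It can also be said that heavy selective stopping would show elsewhere. If six of 20 stopped and missed the final forms, the assessment benchmark would reach at most 14/20 = 70% and fail Table 2's threshold. If they left before a third session, attendance would fail too. This stands for heavy stopping. With four stoppers it gives less protection: 16/20 = 80% still passes the acceptable level for assessments, while 12 of 16 would pass the credibility benchmark.

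Three stronger readings are tempting and not supported:

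- That the benchmark cannot answer its own question. The article describes the scale by believability and logic, which participants can rate after seeing the programme. The objection reaches the expectancy half.
- That it duplicates user experience. The two scales are described as measuring different things; a shared timepoint makes overlap likely, not identity.
- That the results cannot inform the later trial. The article says only that results will inform it and plans no specific use of expectancy scores.

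Early impressions may be partly captured, since beta testing collects module ratings and comments and the feasibility trial follows similar procedures. Those are not expectancy scores.

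**Conclusion.** The point holds for expectancy and rests on explicit text: a primary benchmark that includes expectancy is measured once, after the intervention, with no earlier rating. Such a score is open to influence by experienced benefit and overlaps with the satisfaction measure. As retrospective credibility it remains usable.

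The effect on the pass mark is conditional. If only completers are counted, 12 of 16 or 10 of 14 suffices, equal to 60% or 50% of 20 enrolled, against 15 of 20 when everyone is asked and counted. This assumes full enrolment and exclusion of early stoppers. If stopping is unrelated to credibility, the observed share does not shift.

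The defect is confined to one of seven descriptive benchmarks in a single-arm feasibility trial. It should be fixed; it does not undermine the trial as a whole.

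**What to change.** Give the Credibility and Expectancy Questionnaire to every enrolled participant after the orientation session or session 1, and before session 2 unlocks. Base the Table 2 benchmark on that score, with all enrolled as the denominator. Keep the post-intervention administration as a secondary measure, labelled retrospective credibility.

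The cost is one extra short form in REDCap, next to baseline and orientation steps that already exist. The Results section reports that, as of August 2025, intervention content was only starting to be created, so the change looks feasible before phase 2. The downside is small: the early rating reflects only the rationale and the first content, not the whole programme.

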### Data Analysis

#### Phase 1: Focus Groups

We used rapid data analysis during focus groups to enable timely application of key findings to iterative refinement of our prototype and procedures. Next, we will use thematic analysis following a hybrid deductive-inductive approach [67,68] for a deeper analysis to gauge treatment needs, preferences, and perceptions of the intervention. We will analyze qualitative data from the interviews by using NVivo 12, which enables reliability assessment (κ) of theme-coding between independent coders. Coders will discuss and resolve potential discrepancies until they reach agreement and sufficient reliability, indicated by κ>.80. We will use the results to make specific adaptations to the program content and procedures based on focus group data to best meet participants’ needs and challenges.

#### Phase 2: Beta and Feasibility Testing With Exit Interviews

We will use frequency and proportions to assess the feasibility of the recruitment and retention procedures. We will determine treatment satisfaction and credibility by the proportion of participants who score above the scale midpoint in the User Experience Questionnaire [65] and Credibility and Expectancy Questionnaire [66], respectively. See Table 2 for further details on the feasibility, credibility, and acceptability benchmarks, consistent with other established feasibility work [67-69]. We will analyze qualitative data from the exit interviews by using the same procedures described in phase 1.

**Table 2 table2:** Feasibility benchmarks.

Outcome	Acceptable	Excellent
Credibility and expectancy	>70% of the participants with score over scale midpoint.	>75% of the participants with score over scale midpoint.
User experience	>70% of the participants with score over scale midpoint.	>75% of the participants with score over scale midpoint.
Feasibility of recruitment	>70% of eligible participants agree to participate.	At least 80% of eligible participants agree to participate.
Acceptability of treatment	>70% of the participants attend 3 out of 5 sessions.	>80% of the participants attend 3 out of 5 sessions.
Adherence to homework	>70% of the participants practice >1 skill on 3 d/wk.	>80% of participants practice >1 skill on 3 d/wk.
Feasibility of assessments	>70% of the participants have no measures fully missing.	>90% of the participants have no measures fully missing.
Adverse events	Minimal	None

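### The pass mark for credibility/expectancy, user experience and recruitment is ≥70% in the Abstract but >70% in Table 2; for the two questionnaires, 14 of 20 respondents meets one rule and misses the other

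*Protocol article*

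**What the plan says.** The Study Design and Setting section makes the feasibility benchmarks the primary outcomes of phase 2. Their pass marks appear in two places.

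- **Abstract, Methods (inclusive sign).** Recruitment: "recruitment (≥70% of the eligible participants will participate". Credibility and expectancy: "expectancy (≥70% above the Credibility and Expectancy scale’s midpoint". Satisfaction: "satisfaction (≥70% above the User Experience Questionnaire’s midpoint".
- **Data Analysis, Phase 2, Table 2, Acceptable column (strict sign).** Credibility/expectancy and user experience share one wording: ">70% of the participants with score over scale midpoint". Recruitment: ">70% of eligible participants agree to participate".

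The Excellent level for recruitment in Table 2 reads "At least 80% of eligible participants agree to participate", so the table contains inclusive as well as strict wording. On size, Study Design and Setting says "We will then conduct a feasibility trial (up to n=20", which is a ceiling. The Data Analysis text refers the reader to Table 2 for the benchmarks and does not comment on the Abstract's sign.

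**The concern.** Apart from the sign, the definitions of these three benchmarks match: the same outcome, the same 70%, and the same scale midpoint or the same eligible pool. A reader therefore has two pass marks for one primary outcome. In a large trial the difference between ≥ and > would hardly ever matter. Here the planned maximum is 20, and 70% of 20 is a whole number, so a single attainable count separates the two rules. If that count occurred on a questionnaire benchmark, the result could be called met or missed according to the sentence cited, and the choice could be made after the count was known. The article describes these outcomes by frequencies and proportions set against the benchmarks, so the inequality is itself the decision rule.

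This is separate from the acceptability benchmark, where the two places also differ in the number of sessions.

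**Working it through.** The article gives no sample-size or power figure for these benchmarks, so there is no stated calculation to reproduce. The check has three parts.

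**Inputs.** Threshold 70%, inclusive in the Abstract and strict in Table 2. Questionnaire denominator n: the number of respondents, at most 20 in the feasibility trial. Recruitment denominator: the number eligible. The true proportions used below are assumptions; the article gives none.

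**1. Where the two rules differ.** The inclusive rule needs the smallest k with k/n ≥ 0.70; the strict rule needs the smallest k with k/n > 0.70. These differ only if 0.7n is a whole number, that is, if n is a multiple of 10.

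| Respondents n | 0.7n | Minimum k, ≥70% | Minimum k, >70% |
|---|---|---|---|
| 18 | 12.6 | 13 | 13 |
| 19 | 13.3 | 14 | 14 |
| 20 | 14.0 | 14 | 15 |

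For every n from 11 to 19 the minimum counts are the same. At n = 20, 14/20 = 70.0% passes one rule and fails the other.

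The sign also sets the width of the Acceptable band for the questionnaires. The Excellent level is above 75%; 15/20 = 75.0% does not reach it and 16/20 = 80.0% does. Acceptable but not Excellent is therefore 14 or 15 of 20 under the Abstract's sign, and only 15 of 20 under Table 2's.

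**2. How often the conflict would decide a questionnaire benchmark, given exactly 20 respondents.** With X binomial(20, p), the chance of the disputed count is

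P(X = 14) = C(20,14) · p^14 · (1 − p)^6, with C(20,14) = 38,760.

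This equals P(X ≥ 14) − P(X ≥ 15), the difference between the two pass probabilities.

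| Assumed true proportion p | P(pass), ≥70% | P(pass), >70% | P(exactly 14/20) |
|---|---|---|---|
| 0.70 | 0.608 | 0.416 | 0.192 |
| 0.75 | 0.786 | 0.617 | 0.169 |
| 0.80 | 0.913 | 0.804 | 0.109 |
| 0.85 | 0.978 | 0.933 | 0.045 |

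**3. Recruitment.** Its proportion is the number agreeing divided by the number eligible. If 20 agree and enrol, a conflict would need 20/0.70 = 28.57 eligible people, which is not a whole number. The nearest cases are 20/28 = 71.4%, which passes both rules, and 20/29 = 69.0%, which fails both. A conflict needs exactly 70% of a multiple of ten: 7 of 10, 14 of 20, 21 of 30 or 28 of 40 eligible people agreeing.

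**The case against.** The case for leaving this alone has four parts.

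**Table 2 can be identified as the operative rule.** The Data Analysis section points to it, and an abstract is a summary. This makes the choice of rule less open than it first looks, and supports aligning the Abstract to the table. It does not remove the contradiction: both statements are current and neither is marked as approximate. Because the recruitment row of Table 2 uses inclusive wording for its higher level, the strict sign cannot safely be read as loose notation for ≥.

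**Twenty is a ceiling.** Both questionnaires are given once, immediately after the intervention. If the denominator is respondents, one missing form takes it to 19, where the rules agree. This stands, and it limits the point to full response at full enrolment. If participants without a form were instead counted as not above the midpoint, the denominator would remain 20, which is one reason to state it.

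**The probabilities fall if the programme does well.** The Discussion hypothesises high feasibility. The chance of exactly 14/20 drops to 0.045 at a true 85% and about 0.009 at 90%. This also stands. The range belongs with the finding, not one value at 70%.

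**The benchmarks are descriptive.** There is no test, alpha or stated stop/go rule, and a report of 14/20 would be visible to any reader. That keeps the severity low, but the label of met or missed on a primary outcome would still depend on the sign.

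A reader might also infer more than the document supports:

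- *That recruitment conflicts at 20 enrolled.* It does not, because its denominator is the number eligible.
- *That the beta test of up to 10 has the same problem, at 7 against 8.* The arithmetic is right, but the Beta Testing section describes module ratings, text feedback and exit interviews. The questionnaire battery appears under Feasibility Testing. Table 2 sits under a heading covering both parts, yet no section describes giving these two questionnaires to beta testers.
- *That there is a 35% chance of at least one questionnaire landing on 14/20.* The figure is 1 − (1 − 0.1916)² = 0.347. It needs a true proportion of exactly 70% on both scales, 20 respondents on both, and independence between two scales answered by the same people.
- *That the false-pass rate doubles.* At an assumed true 60% the pass probabilities are 0.250 and 0.126, but calling these false passes presumes a null value that the article does not set.

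**Conclusion.** Wrong as written, minor: an inconsistent decision threshold. For all three benchmarks the Abstract and Table 2 give different signs. The consequence at the planned maximum is confined to the two questionnaire benchmarks, where exactly one count, 14 of 20, changes the result. Given 20 respondents and independent responses between participants, the choice of sign shifts the chance of passing either benchmark by about 19, 17, 11 and 5 percentage points at assumed true proportions of 70%, 75%, 80% and 85%. With 11 to 19 respondents it shifts nothing. For recruitment the contradiction in wording is real, but it affects the result only if exactly 70% of a multiple of ten eligible people agree.

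**What to change.** Before any phase 2 data are seen:

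1. Choose one inequality and use it in the Abstract, in Table 2 and wherever else the benchmark is stated. Table 2's >70% is the more detailed statement and the natural one to keep.
2. State the denominator for each benchmark: respondents or all enrolled for the two questionnaires, and eligible people for recruitment.
3. For credibility/expectancy and user experience only, add the count at full response: at least 15 of 20 respondents. Do not attach this count to recruitment, whose denominator is not the 20 enrolled.

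The Results section reports that, as of August 2025, intervention content was only starting to be created, and it expects the phase 2 analysis in 2026, so on that timetable the correction can precede the data. The cost is wording alone. The downside of keeping the strict sign is that the benchmarks become slightly harder to meet than the Abstract implies, by one participant when there are 20 respondents.

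### The primary acceptability benchmark is stated in two incompatible ways (abstract: complete at least 4, or 5, sessions; Table 2: attend 3 of 5), so the same data can pass one and fail the other

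*Protocol article*

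**What the plan says.** Both the abstract ("The primary outcomes are feasibility benchmarks") and the section Study Design and Setting ("For phase 2, the primary outcomes are feasibility benchmarks") make the feasibility benchmarks primary, and both lists include acceptability. The intervention "consists of 5 sessions (Table 1").

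The benchmark itself is given twice:

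- Abstract, Methods: "acceptability (≥70% of the participants complete ≥4 or 5 sessions").
- Table 2, in the Phase 2 part of Data Analysis: acceptable if ">70% of the participants attend 3 out of 5 sessions"; excellent if ">80% of the participants attend 3 out of 5 sessions".

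The Phase 2 analysis text refers the reader to Table 2 for the benchmarks. The section Treatment Delivery and Protocol Adherence adds that platform tracking will be used to "evaluate participation, even on partially completed sessions", to make the evaluation of attendance more accurate.

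**The concern.** A primary outcome with two pass rules has no determinate result. Three things differ at once: the number of sessions, whether a session must be completed or only attended, and whether exactly 70% is enough. The article does not assign the rules to different stages or purposes. The excellent tier of Table 2 does not explain the abstract's figure either, because it also uses 3 of 5 and only raises the percentage.

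The wording in the abstract may be a slip for at least 4 of 5, but that reading still conflicts with 3 of 5. As written, a reader of the results could not tell whether the benchmark had been met, and the choice of rule could be made after the data are known. These benchmarks are the trial's stated criteria for feasibility, and its results are meant to inform a later efficacy trial.

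**Working it through.** The article gives no calculation for this benchmark, so there is no figure to reproduce. The check has two parts; only the second needs an assumption.

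**Inputs.** 5 sessions (The Face-Forward-Web Intervention); up to 20 participants in the feasibility trial and up to 10 in beta testing (abstract); the thresholds quoted above. Attending 3 of 5 is read as at least 3.

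**1. Pass counts and examples (no dropout model)**

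| Rule | Sessions | Needed of 20 | Needed of 10 |
|---|---|---|---|
| Abstract, at least 70% | at least 4 (or all 5) | 14 | 7 |
| Table 2 acceptable, more than 70% | at least 3 | 15 | 8 |
| Table 2 excellent, more than 80% | at least 3 | 17 | 9 |

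- *Table 2 passes, abstract fails.* 17 of 20 reach three sessions and 12 of 20 complete four. 17/20 = 85%, above 80%, so Table 2 says excellent. 12/20 = 60%, below 70%, so the abstract rule fails.
- *Abstract passes, Table 2 fails.* 14 of 20 complete four or more and the other six stop before session 3. 14/20 = 70%, which meets at least 70% but is not more than 70%.

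If attending and completing are counted alike, everyone with four sessions also has three. The second kind of disagreement then comes only from the inequality.

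**2. How often the rules disagree (assumed dropout)**

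Assume that each participant goes on to each session, the first included, with constant probability c. Then P(at least 3) = c³ and P(at least 4) = c⁴. The number reaching three sessions is binomial(20, c³) and, of those, the number reaching four is binomial with probability c. Summing the joint probabilities over the pass counts above gives:

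| c | c³ | c⁴ | Table 2 passes, abstract fails | Abstract passes, Table 2 fails | Total |
|---|---|---|---|---|---|
| 0.85 | 0.614 | 0.522 | 8.4% | 1.4% | 9.8% |
| 0.88 | 0.681 | 0.600 | 13.0% | 3.1% | 16.2% |
| 0.90 | 0.729 | 0.656 | 13.4% | 4.2% | 17.6% |
| 0.92 | 0.779 | 0.716 | 10.2% | 4.3% | 14.5% |
| 0.95 | 0.857 | 0.815 | 2.5% | 1.8% | 4.4% |

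(Totals were rounded after summing.) At c = 0.90 the chance of passing is 53.2% under Table 2 and 43.9% under the abstract at four sessions. It is 22.3% if the abstract is read as requiring all five.

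*Sensitivity to the model.* In expected proportions alone, the verdicts split when c³ > 0.70 and c⁴ < 0.70. That is dropout between 1 − 0.70^(1/4) = 8.5% and 1 − 0.70^(1/3) = 11.2% per session. If everyone starts session 1, the exponents become 2 and 3 and the band moves to 11.2% to 1 − 0.70^(1/2) = 16.3%.

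**The case against.** The strongest reply is that an abstract is only a summary. The analysis section points to Table 2, so Table 2 is arguably the operative rule and the repair may be no more than a correction to the abstract. The study is also small, has seven benchmark domains and ties no formal go/no-go rule to acceptability. This limits the consequences and bears on which text should change. It does not remove the conflict: both statements are current, both describe a primary outcome, and nothing says which prevails. A fuller protocol could agree with at most one of them.

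Some stronger readings are tempting, but the documents do not support them:

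- *That partly completed sessions count as attended.* The article says partial use is tracked, not that it counts. Each session opens only after the previous session's quiz is completed, so a participant who opens session 3 has already completed two. The gap between attending and completing is at most one session.
- *That Table 2 would declare success although most participants never reach sessions 4 and 5.* The wording allows this arithmetically, but nothing shows that it is likely. With 10% dropout per session, 65.6% still reach session 4.
- *That the rules split over a wide, realistic range of dropout.* The article gives no dropout rate, and in expected proportions the band is narrow. At 8% dropout both rules pass (77.9% and 71.6%); at 12% both fail (68.1% and 60.0%).
- *That the authors mean to choose the rule afterwards.* Nothing suggests it; the text merely leaves it possible.

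**Conclusion.** The concern holds as an internal contradiction in the definition of a primary outcome. It rests on the two statements alone and needs no assumption about dropout: with 20 participants, plausible-looking counts can give opposite verdicts in either direction. The frequency, roughly 4% to 18% of trials of 20, rests on an assumed constant continuation of 0.85 to 0.95 per session, possible loss before session 1, and attending and completing counted alike. It is an illustration, not a forecast. Most of the disagreement runs one way, with Table 2 passing and the abstract failing. The documents do not establish which rule is intended. The matter should be settled before phase 2 enrolment; the Results section says that, as of August 2025, the team was only starting to create the intervention content.

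**What to change.** Before the first phase 2 participant is enrolled, state one rule in the abstract and in both tiers of Table 2, fixing:

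1. **Session count:** one number. At least 4 of 5 is one option, since it requires reaching the later skills sessions; its downside is a benchmark that is harder to meet than 3 of 5. Keeping 3 of 5 and correcting the abstract is equally coherent. Whichever is chosen, write it with *at least*.
2. **Inequality:** at least 70% or more than 70%. At 20 participants this decides whether 14 or 15 is needed.
3. **Event:** for example, end-of-session quiz completed, which the platform already uses to unlock the next session.
4. **Denominator:** all enrolled participants.

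Report the other session count, and partial use, descriptively.

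The cost is a few words in the abstract and in two cells of Table 2, with no new data collection. If the stricter count is chosen, the trial is less likely to meet its benchmark: under the model above at c = 0.90 and with the inequalities as now written, the chance of passing is 43.9% rather than 53.2%.
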